# PRO*BPD: effectiveness of outpatient treatment programs for borderline personality disorder: a comparison of Schema therapy and dialectical behavior therapy: study protocol for a randomized trial

**DOI:** 10.1186/s12888-018-1905-6

**Published:** 2018-10-19

**Keywords:** Borderline personality disorder, Psychotherapy, Dialectical behavior therapy, Schema therapy, Randomized controlled trial, Economic evaluation, Clinical effectiveness

## Abstract

**Background:**

Borderline Personality Disorder (BPD) is a severe mental illness that is associated with low quality of life, low psychosocial functioning, and high societal costs. Treatments for BPD have improved in the last decades. Dialectical behavior therapy (DBT) and Schema therapy (ST) have demonstrated efficacy in reducing BPD symptoms and costs. However, research has not compared these two treatment approaches. In addition, there is a lack of ‘real world studies’ that replicate positive findings in regular mental healthcare settings. Thus, the PROgrams for Borderline Personality Disorder (PRO*BPD) study will compare the (cost-) effectiveness of DBT and ST in structured outpatient treatment programs in the routine clinical setting of an outpatient clinic.

**Methods/Design:**

We aim to recruit 160 BPD patients, who will be randomly assigned to either DBT or ST. In both conditions, patients receive one group therapy and one individual therapy session/week for a maximum of 18 months. Both treatment programs have similar frameworks, which guarantee clinical equipoise. The primary outcome is a reduction of BPD-symptoms. Also, the costs related to BPD are assessed and an economic evaluation is performed from a societal perspective. Secondary outcomes examine other measures of BPD-typical and general psychopathology, comorbidity, quality of life, psychosocial functioning and participation. Data are collected prior to the beginning therapy and every six months until the end of therapy, as well as at six months, one year and two years of follow-up after the end of therapy. Finally, we conduct a qualitative study to understand patients’ experiences with the two methods.

**Discussion:**

The PRO*BPD study is the first randomized trial to compare the (cost-) effectiveness of DBT and ST. By examining the clinical effectiveness of a broad spectrum of outcome parameters, conducting an economic evaluation and assessing patients’ experiences, this study will significantly advance our knowledge on psychotherapy for BPD and will provide insight into the treatment approaches that should be offered to different BPD patients from clinical, economic and stakeholder’s perspectives.

**Trial registration:**

German Clinical Trial Register, DRKS00011534, Date of registration: 11/01/2017, retrospectively registered.

## Background

Borderline Personality Disorder (BPD) is a prevalent, severe, complex mental illness that is characterized by a pervasive pattern of instability in interpersonal relationships, self-image, affect, and behavioral dysregulation [1]. Patients with BPD suffer from an array of comorbidities with other mental disorders, e.g., depression, anxiety, substance use and other personality disorders [2]. BPD affects every aspect of life (e.g., relationships with others, education, work, self-care) and thus is associated with significant impairments in quality of life across mental, social and physical dimensions [3]; persistent poor social functioning and participation [4–8]; and high societal costs [9, 10].

The prevalence of BPD is estimated to be 1.1% in the general population [11]. BPD is one of the most frequent PD in clinical populations and is diagnosed in up to 10% of outpatient and 25% of inpatient populations [12–14]. Individuals who have BPD often experience crises with self-harm or suicide attempts, and thus show an intensive use of health services and high costs [11, 15–17]. The direct health care costs that result from BPD are markedly higher than those for depression (e.g., 11,817 € vs. 6058 € per patient two years after an index diagnosis in a German study) [17]. A recent systematic review and cost offset analysis from economic evaluations revealed that empirically supported psychological treatments for BPD can massively reduce those costs [16].

Longitudinal research has yielded important findings on the course of BPD: the symptoms that are related to impulsivity, such as self-harm and suicidality, are more quickly resolved. By contrast, affective symptoms that reflect chronic dysphoria, such as loneliness and emptiness, are more stable [18]. On the one hand, high rates of remission have been found after several years, in which patients no longer meet the full spectrum of criteria for BPD. However, severe impairments in social functioning and quality of life usually persist [5, 8].

Not long ago, BPD was viewed as an ‘untreatable’ disorder; however, it can now be successfully treated with several empirically supported psychotherapeutic methods from different therapeutic orientations that were specifically designed for BPD [19–21]. These treatments include Dialectical Behavior Therapy (DBT) [22, 23] and Schema therapy (ST) [24, 25], which are grounded in cognitive behavior therapy.

To date, DBT is the most frequently evaluated psychotherapy for BPD: A recent meta-analysis, a Cochrane Review on general psychotherapy for BPD, and a meta-analysis on DBT only summarize the evidence of the efficacy of DBT in treating patients with BPD, which has been demonstrated in several randomized controlled trials (RCT) [20, 26, 27]. The primary outcomes are decreases in suicidality, self-injuring and impulsive behaviors, emergency room visits and inpatient admissions. Effectiveness studies under routine clinical care conditions in Germany and Australia had comparable results and suggest that the findings generalize to ‘real world’ conditions [28, 29]. The German study also found that the DBT program was associated with substantial cost savings [30]. DBT has also been effective in treating BPD with comorbidities and other psychiatric conditions, such as substance misuse [31–33], eating disorders [34–36], posttraumatic stress disorder [37–40], or depression [41].

ST shows promise for treating BPD as it was effective in reducing all BPD criteria and led to substantial improvements in quality of life [42, 43]. Two RCTs [44, 45], one case series [46], five open pilot studies [47–49] and one implementation study [50] demonstrated decreases in all nine BPD symptoms, general psychiatric symptoms, and quality of life, as well as low treatment drop out. In the first Dutch RCT ST was compared with transference focused therapy (TFP), both offered in an individual design. ST showed better treatment retention, and in the intention-to-treat-analysis it was clinically more effective than TFP [45]. Also, ST was more cost-effective [51]. A pre-post comparison demonstrated successful implementation of individual ST under routine clinical care conditions [50]. A group format (Group schema therapy, GST) was developed by Farrell and Shaw [52] and was successfully tested in an RCT in the United States: Patients who received GST showed no drop-out, high BPD remission rates, significant reductions in BPD-typical and general psychiatric symptoms as well as improvements in psychosocial functioning, with large effect sizes after only 8 months. Two outpatient pilot studies on GST in the Netherlands [47] and Germany [48] used GST in combination with individual ST and found substantial improvements in BPD-symptoms, general psychopathology, quality of life and happiness. To systematically investigate the clinical effectiveness and cost-effectiveness of GST for BPD and to test different formats of GST (GST only vs. a combination of GST with individual ST), a large, international, multicenter RCT on GST for BPD is currently in progress [53]. A meta-analysis from 2013 (including all published outpatient studies through 2013, which are all mentioned above, except for [48, 49]) revealed an overall effect size of d = 2.38 for pre-post change and an overall drop-out rate of 10% for ST in BPD patients. This is a very low drop-out rate compared to the average drop-out rate of 25% for BPD patients for interventions with a minimum duration of 12 months [54].

In sum, there are promising findings on the clinical efficacy and effectiveness of DBT and ST in treating BPD [20]. Moreover, both treatments lead to impressive reductions in direct and indirect health care costs (approx. 10,000 € per patient per year) [30, 51]. However, research has not yet compared these two methods. A treatment comparison would be interesting for psychotherapy research because both treatments have different approaches to treating BPD and focus on different techniques, despite several common factors (see also methods and a detailed overview in [55]).

The objective of this study is to compare the (cost)-effectiveness of DBT and ST in patients who have BPD. The PRO*BPD trial is the first randomized trial to compare these two methods. The primary hypothesis is that DBT and ST significantly differ in reducing BPD-severity (two-sided hypothesis). A two-sided hypothesis was chosen because information from literature does not allow predictions on the directionality of the difference (see discussion for more information on this theme).

In addition, we evaluate the costs and perform an economic evaluation from a societal perspective. Thus, a secondary hypothesis is that the two methods differ in their cost-effectiveness. In a budget-constrained health care system, there is an urgent need for detailed information on the costs and benefits of an intervention to inform decisions on resource allocation. A major challenge for BPD-specific psychotherapy is to demonstrate that the treatment leads above and beyond reductions in external BPD-symptoms (e.g., self-harm, suicide attempts or impulsive behavior) also to improvements in internal BPD-symptoms (e.g., chronic dysphoria, loneliness or feeling empty), as well as associated difficulties, including global psychosocial functioning, comorbid disorders, and quality of life. Thus, the outcomes of this study address not only BPD-symptoms but also the quality of life, psychosocial function and participation, general psychopathology and other psychiatric disorders. Further secondary hypotheses involve different effects of the two treatments in the different BPD symptoms and other secondary outcomes. Also, there might be different effects in subgroups of patients with BPD (e.g., different effects based on comorbid disorders or patterns of BPD symptoms) which will help to advance our knowledge about which treatment should be offered to which patient. More support from literature and discussion of the secondary hypotheses can be found in the discussion section.

We study moderating and mediating variables (e.g., sex, age, the severity of BPD-symptoms, comorbidity, traumatic experiences during childhood, experiential avoidance) through exploratory data analysis. Furthermore, we conduct a qualitative study on patients’ experiences with the two treatment methods.

The PRO*BPD study is conducted in the routine clinical setting of an outpatient clinic and responds to the call for ‘real world’-studies. As such, we use minimal exclusion criteria, set low barriers to patient participation and guarantee the clinical equipoise of the two treatment programs. Thus, we include BPD patients with the entire range of mental disorder comorbidity and high BPD severity and minimize resistance for participating in a clinical trial with randomization.

## Method/design

### Design

The study design is a randomized trial with two active groups (a treatment program for 1.5 years with either DBT or ST). This trial includes an evaluation of clinical effectiveness, an economic evaluation and qualitative research on patients’ perspectives of the two methods. Independent assessors collect data to evaluate the clinical effectiveness and cost-effectiveness with semi-structured interviews and self-report measures on BPD-specific symptoms, general psychopathology and BPD-associated psychopathology (e.g., dissociation, emotional dysregulation, depression), the course of comorbid disorders, quality of life, psychosocial functioning and participation and administer a structured interview to assess costs. Assessors are blind to the patients’ treatment condition for all outcome measures, only for assessment of treatment costs blinding is not possible. Data are collected at baseline and every six months until the end of treatment and continues 6, 12 and 24 months after the end of therapy as a naturalistic follow-up. In this follow-up phase, patients will be provided with supportive care in our center as indicated and can seek additional treatments outside of our center if they believe that they need more help. The data will include treatment participation in the follow-up-phase. Complete allocation concealment is not possible in a psychotherapy effectiveness study. To reduce bias, we employ partial allocation concealment by shifting the patients’ focus from the comparison of the two treatment methods. Because there is a comparison, patients could believe that one of the two methods is better than the other, which could lead to bias. Thus, the patients are not aware of the primary hypothesis in this study. The patients are informed (in the written and verbal patient study information) that the primary intention of the research is on the processes and predictors of therapy outcomes and that randomization is necessary for an unbiased distribution of participants across the two treatments to allow for unbiased tests of predictors and processes.

The PRO*BPD trial adheres to the SPIRIT guidelines and methodology [56]. For an overview of the study design, see the flow chart for enrollment, intervention, and assessment that is shown in Fig. 1.

**Fig. 1 Fig1:**
[figure not shown]
Flow chart of the study design. DBT = dialectical behavior therapy; ST = schema therapy, BPDSI = Borderline Personality Disorder Severity Index; BPD = Borderline Personality Disorder

#### Recruitment and setting

The PRO*BPD study is performed in the outpatient clinic of the Department of Psychiatry and Psychotherapy at Lübeck University, Germany. The Department of Psychiatry treats more than 450 BPD patients/year (internal statistics) and has extensive experience in treating and researching BPD [48, 55, 57–59]. DBT has been used in Lübeck since 1999, while ST has been offered since 2009. Patients are included via the standard pathways of care in the clinic (inpatient and outpatient clinics, emergency room, and patients sent from other departments in the University Hospital). Potential participants are verbally informed about the study and are provided with written information. If they agree to participate they complete a signed written informed consent and the patient is invited for a screening to assess the in- and exclusion criteria.

#### Participants

Patients aged between 18 and 65 years are eligible if they (1) have a primary diagnosis of BPD (diagnosed with the Structural Clinical Interview for DSM-IV for Axis II; SCID II-Interview), (2) have a BPD severity score that is greater than > 20 points on the Borderline Personality Disorder Severity Index (BPDSI), Version 4 [60], (3) are willing to participate in the study (informed consent), and (4) are willing and able to remain in the study for 1.5 years and reliably participate in therapy (no relocation plans etc.). Exclusion criteria are (1) a major psychotic disorder (lifetime diagnosis), (2) intellectual deficits (IQ < 85), (3) poor German language skills, and (4) acute severe substance dependence that causes severe cognitive restrictions during therapy and necessitates detoxification treatment. Participation is possible after detoxification and a four-week period of abstinence. Patients who have cannabis dependence can participate if they commit to working on abstinence during treatment. We decided on a limited number of exclusion criteria to ensure high external validity and the generalizability of the results.

#### Sample size

The primary variable for calculating the sample size is the BPDSI total score. The sample size calculation is based on the number of participants that are needed to detect a clinically significant difference between the two conditions. Although the meta-analyses on DBT demonstrated global changes in effect sizes (ES) of d = 0.5 [27] and ST had a higher change in ES for borderline-specific symptoms (d = 2,96 [45] and d = 2.81 [44]), these cannot reliably be compared because they reflect different samples and outcome instruments, and there has been no direct comparison between the two methods. Therefore, we chose a medium ES of d = 0.5 for detecting group differences for the sample size calculation. Detecting a difference with this ES could strongly influence clinical decision making. As such, *n* = 64 patients per condition are required to detect group differences with a Type I error of 5% and a power of 80% (Type II error = 20%). Assuming an attrition rate of 20%, we will recruit *n* = 160 patients.

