#### Randomization

Patients are informed about both treatment approaches and are willing to participate in a random assignment. Randomization is conducted in two patient pairs with a 50–50% assignment to one of the two therapeutic modalities using the program BiAS 11.02 [61]. Randomization is stratified by gender to control for the gender distribution in each treatment modality.

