### Treatments

#### Common framework

The structural conditions of both treatment programs are as similar as possible to guarantee clinical equipoise: In both groups, patients receive a combined program of one group therapy session (120 min) and one individual therapy session (60 min) per week for a maximum of 18 months. Patients receive 4–10 weekly individual sessions before beginning the 18 months combined program to become accustomed to their individual therapist and the treatment model, as well as to be prepared for the group sessions. The exact number of individual sessions, which a patient receives, preceding the combined treatment program, is determined by the availability of treatment slots of the individual therapist. With absences that are due to illness, holidays or other disruptions, we estimate that each patient has an average therapy dose of 65 individual sessions and 60 group sessions. The groups consist of a maximum of ten patients and are conducted by two therapists. Groups are offered in a semi-open format. Thus, when treatment slots for patients are available (e.g., because of treatment drop-out or early success of a patient), new patients will enter the group. Thus, this format compensates for dropout and allows new study patients to begin more quickly than in a closed group. The time spots where new patients enter the group will be planned between research and therapist team and are dependent on a variety of points: available treatment slots in the group treatment and a time point that is suitable from a therapeutic stance to include new patients (e.g. after ‘group holiday’ or termination of a specific therapeutic theme), availability of an individual therapist to offer weekly individual sessions with at least four sessions preceding entry of the patient in the group treatment and completeness of baseline assessments. Eligible patients who are not able to attend group sessions due to family, professional or educational duties are included in the trial and are provided individual therapy only. In both conditions, patients can call their individual therapists outside of the sessions for support (a major component in DBT and to a lesser degree in ST). However, telephone support by the individual therapist is limited to office hours (which is normally not the case in DBT) to respect the participating therapists’ personal boundaries and to provide the same conditions for each patient. Outside of office hours, the psychiatric emergency service of our department is available for patients at any time. All patients also receive psychiatric management in our center. Additional medication is prescribed as needed according to national guidelines. According to our experience with BPD patients, this will reduce pre-existing polypharmacotherapy. Medication will be statistically controlled for in the data analyses.

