#### Statistical analyses of the clinical effectiveness study

Data analyses will be performed based on the intention-to-treat principle (including all patients regardless of whether they drop out from treatment or not) and will use all available data. Data for the primary and most secondary outcome measures will be analyzed with multilevel analysis to compare DBT to ST (mixed regression models for repeated measures). Time will be modelled according to the best model fit, e.g., a linear, logarithmic, or a segmented development of scores over time. The treatment by time interaction will be the primary test for treatment differences. We will use a piece-wise regression model if preliminary inspection of the data indicate that the time development during treatment has a different slope than during the follow-up period. If the time-development is better represented by a continuous equation (e.g., time, or SQRT (time), or log (time)) than we will do sensitivity tests of the treatment x time interaction for the treatment period, in addition to the test for the whole assessment period. We will also examine the between group differences at specific time-points, e.g., at the end of treatment and the final follow-up. For categorical outcome variables, counts appropriate forms of mixed regression will be chosen, with attention to non-normal residuals (negative binomial, Poisson, and gamma, etc.). Mixed regression methods will also be used to identify predictors/moderators that are related to treatment outcomes. Survival analysis will be used to analyze treatment retention.

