Another strength of this trial is the multidimensional assessment of outcomes with a clinical and a cost-effectiveness trial as well as a qualitative interview study that examines the perspectives and experiences of patients who are treated with the two methods.

It is important to discuss several limitations and potential pitfalls. First, the sample size was calculated to reliably detect differential treatment effects for the primary outcome with a medium effect size or larger. However, with two bona fide psychotherapies, there could be smaller effects that might not be detected. However, the study contributes to building a database of treatments comparisons for BPD that meta-analytic techniques will use to document comparisons of different treatments. Second, we decided to provide two active groups and no control condition without treatment or treatment as usual. The study is deliberately designed as an effectiveness and not an efficacy study. However, when both treatments lead to improvements but do not have significantly different effects, the absence of an inactive control condition does not exclude the possibility that unspecific factors, such as time, may have led to the improvements. However, in addition to several serious ethical consequences, a control group would endanger the representativeness of the study group, which was explained above.

The PRO*BPD study is only conducted in one center at Lübeck University, which is a strength of the study because organizational/logistic issues and adherence to the research protocol is easier than in a multicenter trial. On the other hand, the monocentric design might have implications for generalizability and external validity. One possible barrier to the generalizability of our study population may be its unusually high severity and comorbidity compared to the general BPD population in Germany. This is because the University Hospital setting is utilized by a high number of patients who have complex BPD and high comorbidities, who cannot find access to therapy elsewhere (i.e., in private psychotherapy practices). Nevertheless, this specific group continues to lack access to sustainable treatment and causes immense health care costs due to their frequent and lengthy inpatient treatments and low psychosocial functioning.

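### The 80% power at 64 per arm makes no allowance for patients sharing therapy groups and therapists, so on its own basis it holds only if that clustering is negligible

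*Protocol article*

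**What the plan says.** Sample size section: "The primary variable for calculating the sample size is the BPDSI total score", and "we chose a medium ES of d = 0.5 for detecting group differences for the sample size calculation". From this, "64 patients per condition are required to detect group differences with a Type I error of 5% and a power of 80" per cent, and an assumed 20% attrition takes the total to 160. The test is two-sided (Background: "The primary hypothesis is that DBT and ST significantly differ in reducing BPD-severity (two-sided hypothesis") and allocation is equal (Randomization: "with a 50–50% assignment to one of the two therapeutic modalities").

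Common framework section: each patient has weekly individual therapy plus weekly group therapy. "The groups consist of a maximum of ten patients and are conducted by two therapists". Groups are semi-open, so newcomers fill places as they become free. Eligible patients who cannot attend a group receive individual therapy only. Supervision is organised by method, and the Discussion describes two therapist groups, each with allegiance to its own method.

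Statistical analyses of the clinical effectiveness study: the primary outcome is "analyzed with multilevel analysis to compare DBT to ST (mixed regression models for repeated measures"), and the primary test is the treatment by time interaction. Neither therapist nor therapy group is mentioned.

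The limitations in the Discussion say that "the sample size was calculated to reliably detect differential treatment effects for the primary outcome with a medium effect size or larger". They raise the possibility of smaller true effects, but not clustering.

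**The concern.** Patients who share a group or a therapist tend to have more similar outcomes than patients who do not. Here those clusters appear to lie within arm: a group delivers one method, and the therapists are described as two method-specific teams. The correlation therefore adds directly to the variance of the difference between arms, and randomizing individual patients does not remove it.

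Two things are at stake. The first is the power claim, which is made in this article and which no later document can change for 64 patients per arm. The article itself regards no difference on the primary outcome as a probable result, so readers will use the 80% to judge how informative a null finding is. The second is the error rate. If the eventual model omitted both therapist and group, a good or poor group or therapist could pass for a difference between DBT and ST.

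**Working it through.** **Inputs from the article.** d = 0.5, two-sided alpha 0.05, power 80%, 1:1 allocation, 64 analysed per arm, 20% attrition, at most 10 patients in a group at any one time.

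**Inputs assumed.** The article gives no ICC and no number of patients per cluster. I use ICC 0.01, 0.05 and 0.10, with m = 8 or m = 10 analysed patients per group.

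**Step 1: reproduce the plan's figure.** A two-sample t-test for independent patients needs n = 63.77, so 64 per arm, with power 80.1% at 64. Attrition: 2 × 64 / 0.8 = 160. Both figures reproduce exactly, so no clustering allowance is hidden in either.

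**Step 2: design effect and power.** DE = 1 + (m − 1) × ICC, and effective n per arm = 64 / DE. For example, with m = 10 and ICC 0.05: DE = 1 + 9 × 0.05 = 1.45 and effective n = 64 / 1.45 = 44.1. Power is computed from the noncentral t with noncentrality 0.5 × √(effective n / 2), here 0.5 × √22.05 = 2.35. It is given twice:
- with patient-level degrees of freedom, which is optimistic;
- with cluster-level degrees of freedom, 2 × (64/m − 1), which is 14 for m = 8 and 10.8 for m = 10.

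**Step 3: type I error if clustering is left out of the model.** The true standard error is √DE times the model's, so the actual two-sided error is 2 × [1 − Φ(1.96 / √DE)].

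| m | ICC | DE | Effective n per arm | Power, patient-level df | Power, cluster-level df | Type I error if clustering omitted |
|---|---|---|---|---|---|---|
| 8 | 0.01 | 1.07 | 59.8 | 77.4% | 72.0% | 5.8% |
| 8 | 0.05 | 1.35 | 47.4 | 67.3% | 62.0% | 9.2% |
| 8 | 0.10 | 1.70 | 37.6 | 57.2% | 52.4% | 13.3% |
| 10 | 0.01 | 1.09 | 58.7 | 76.6% | 69.3% | 6.0% |
| 10 | 0.05 | 1.45 | 44.1 | 64.2% | 57.1% | 10.4% |
| 10 | 0.10 | 1.90 | 33.7 | 52.5% | 46.4% | 15.5% |

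**Step 4: turnover.** Ten is the maximum at one time, not over the life of a semi-open group. If 20 analysed patients passed through each group, ICC 0.05 gives DE = 1 + 19 × 0.05 = 1.95, power 51.4% with patient-level df, and type I error 16.0% if clustering is omitted.

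**Step 5: possible recovery.** If the longitudinal model gains precision as a baseline-adjusted analysis would, the variance is multiplied by 1 − r². With an assumed r = 0.5 (factor 0.75), m = 10 and patient-level df, power is 87.5%, 76.7% and 64.9% at ICC 0.01, 0.05 and 0.10. The loss is made good only at the smallest ICC.

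**The case against.** **The model may already carry these levels.** A reader might infer that the primary model treats patients as independent and that its standard errors are too small. The article does not support that. It names repeated measures, but it lists no random effects and rules none out. A multilevel model can hold therapist and group terms, and the random-effects structure is commonly fixed in an analysis plan, which is not shown. This objection stands: the type I error figures apply only if those levels are omitted. It does not touch the sample size, which is stated in full and contains no design effect.

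**The loss may be small.** It depends on figures the article does not give. At ICC 0.01 with 8 per group it is about 3 points with patient-level df, though about 8 with cluster-level df. The planned test is also a treatment by time interaction, so the ICC that matters is that of change over time, and the repeated measurements may be more efficient than a t-test. Dropouts contribute data as well: as an upper bound, if all 80 per arm contributed fully, power at m = 10 (patient-level df) would be 85%, 74% and 62%. All of this is fair, and it means one cannot say flatly that 80% power is not delivered. But the Sample size section claims none of these gains, and at an ICC of 0.05 or more with 10 per group neither gain alone restores 80%.

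**Clustering by group is not clean.** Semi-open membership overlaps in time, and patients without group therapy share only a therapist. With few groups per arm, a group variance is hard to estimate. This bears on how the model is written, not on whether the dependence can be ignored.

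**Conclusion.** The point holds for the power statement. The 64 per arm and 160 recruited are the independent-patient figures plus attrition, while the treatment design puts patients in shared groups and under method-specific therapists. On the article's own basis of calculation, 80% holds only if the ICC is near zero.

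The size rests on assumed values. Over ICC 0.01 to 0.10, power at d = 0.5 is about 57% to 77% with 8 per group and 53% to 77% with 10 (patient-level df), or 52% to 72% and 46% to 69% with cluster-level df. Higher turnover through the groups lowers these figures; baseline adjustment may raise them. That the clusters lie within arm is a reading of the method-specific supervision and therapist teams, since the article does not say outright that no therapist works in both arms.

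Inflated type I error, about 6% to 13% with 8 per group and 6% to 16% with 10, is conditional on therapist and group both being left out of the model. It is not an established fault of the plan.

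**What to change.** 1. In the Sample size section, keep 64 per arm and 160 recruited, but say that the 80% assumes independent patients. Give power as a range over stated ICCs and expected patients per group and per therapist, allowing for turnover and using degrees of freedom that match the planned analysis. The cluster-level columns above show the form for the group part. If a gain from baseline adjustment is claimed, state the assumed correlation.
2. Bring the Discussion's statement about reliably detecting a medium effect into line with that range, and list clustering among the limitations.
3. In the analysis section, specify that the primary mixed model accounts for individual therapist and therapy group within arm, with the group effect applying only to patients who attend a group, and with a small-sample correction to the degrees of freedom (Satterthwaite or Kenward-Roger). Say how overlapping membership of semi-open groups is handled and what is done if a variance component cannot be estimated.

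Cost: wording, and use of therapist and group identifiers in the analysis data (nothing in the article suggests they are not recorded). No extra patients are needed. The price is a less favourable power figure and somewhat wider confidence intervals.
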